## **1.6 Data Safety Monitoring Committee**

In view of the study low risk, as continuous EEG and routine EEG are part of standard clinical care and will be performed according to clinical standards, no specific data safety monitoring committee will be constituted.

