## **6. STUDY DESIGN**

### **6.1 General study design and justification of design**

This will be a multicenter randomized controlled trial assessing prognostic yield of cEEG. While there will be no blinding during the EEG procedure, as this would prove highly impractical in the proposed setting; however, the most important outcomes will be assessed blindly (at 6 month). The study will be carried out in four university hospitals (of the five in Switzerland) and one large regional hospital, located both in the German- and the French-speaking part of the country. An RCT seems the best way to address the primary objective of this study, particularly in terms of minimization of biases.

It is expected to randomize 350 patients over a 2 year-recruiting period. Patients will receive either cEEG or 2 rEEG within the first 48 hours following randomization, and then will be followed up until 6 months after randomization.

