#### **6.2.1. Randomisation**

Randomization (1:1) will be stratified by center and generated using the web-based secuTrial® software. Briefly, randomization by blocks of 4 (2 rEEG and 2 cEEG) will be set up in the system by the data managers of the CTU Lausanne. Using login and password, the local investigator (or his designee) will randomize patients after the eligibility check and just before the intervention by asking the system to provide him/her with a randomization number and intervention allocation. Randomization lists will be kept at the CTU Lausanne during the trial and transferred to the sponsor-coordinating investigator for interim analysis or at the end.

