### 11.2 Determination of Sample Size

According to the only available study broadly addressing this issue , patients with consciousness disorders and cEEG have a 25% mortality (corresponding to 75% survival rate) and patients without cEEG a 39% mortality (implying a 61% survival rate). Considering a power of 0.8, an alpha error of 0.05, and applying a 2-sided test, 2x174 patients (348 in total) would be needed to detect a difference of 61% versus 75% in survival ( $\chi^2$  test for independent samples, Stata version 12, College station, TX). This represents a reasonable difference of non-debatable clinical relevance.

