### 11.3 Statistical criteria of termination of trial

There are no stopping rules for individual participants. The discontinuation criteria for patients are the post hoc or proxy consent refusal/withdrawal, only. An interim analysis of the primary outcome will be performed after recruitment of the first 100 patients if the difference of 14% in survival at six months between the two arms will be met, the study will be interrupted.

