#### **11.4.1. Datasets to be analysed, analysis populations**

The patients data will be analyzed as "intention to monitor EEG", i.e.: forming two groups (one of patients allocated to cEEG, the other to those allocated to rEEG). A per-protocol analysis will also be provided for the primary outcome.

According to current experience with a registry of post-cardiac arrest patients (personal observation in CHUV, Lausanne), subjects lost to follow-up represent 1-2% of the cohort. Available data will be used for secondary outcomes, but subjects will be excluded from analysis of the primary outcome.

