#### **11.4.4. Interim analyses**

An interim analysis of the primary outcome will be performed after recruitment of the first 100 patients: if the difference of 14% in survival at six months between the two arms will be met, the study will be interrupted. This analysis will be conducted by the team of the sponsor-coordinating investigator in Lausanne and using the intermediate clinical trial datasets provided by the data management team of the CRC Lausanne.

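### The interim rule stops the trial on a raw 14-point survival difference in the first 100 patients, about 1.5 standard errors, so it is not an alpha-controlled boundary and the stated 5% alpha and 80% power are not jointly delivered.

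*Protocol*

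**What the plan says.** Protocol section 11.2 sizes the trial for a single comparison: "Considering a power of 0.8, an alpha error of 0.05, and applying a 2-sided test, 2x174 patients (348 in total) would be needed". The planned effect is 61% versus 75% survival, a difference of 14 points. The section makes no allowance for an interim look.

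Section 11.3, on statistical criteria for ending the trial, adds one: "An interim analysis of the primary outcome will be performed after recruitment of the first 100 patients". Sections 11.3 and 11.4.4 then give the same criterion: "if the difference of 14% in survival at six months between the two arms will be met, the study will be interrupted". Neither attaches a significance level, an alpha allocation or a direction. Neither says what is concluded after a stop, or whether patients recruited beyond the first 100 enter the analysis.

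Section 11.4.4 gives the look to the sponsor-coordinating investigator's team, and section 1.6 says that "no specific data safety monitoring committee will be constituted".

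**The concern.** The threshold is the planning effect reused as an observed difference. An effect that 348 patients can detect with 80% power is well within sampling error at 100 patients, so a stop can follow from chance alone. A true effect of the planned size would trigger the rule about half the time, at under a third of the planned information.

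The cost depends on how a stop is read. If the usual 0.05 test is applied at the stop, many truly positive trials end early without a significant result. If the stop is itself the claim, the false positive rate is far above 5%. In both cases the estimate at a stop for benefit is too large on average. The text is worded as an automatic consequence, and no independent body stands between the look and the stop.

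**Working it through.** **Inputs.** Survival 61% and 75%, two-sided alpha 0.05, power 0.80, 174 per arm (section 11.2). Allocation 1:1 (section 6.2.1), so about 50 per arm in the first 100. Accrual: "It is expected to randomize 350 patients over a 2 year-recruiting period" (section 6.1). Loss to follow-up of 1-2% (section 11.4.1) is ignored as negligible.

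**1. The protocol's own figure.** Pooled survival is 0.68.
n = [1.96 × sqrt(2 × 0.68 × 0.32) + 0.8416 × sqrt(0.61 × 0.39 + 0.75 × 0.25)]² / 0.14²
= (1.293 + 0.549)² / 0.0196 = 173.1, so 174 per arm.
This reproduces section 11.2 as a single-look design, with no continuity correction and no interim allowance.

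**2. The boundary as a test.** SE = sqrt(2 × 0.68 × 0.32 / 50) = 0.0933. z = 0.14 / 0.0933 = 1.50, two-sided p = 0.13. For common survival between 61% and 75%, z runs from 1.44 to 1.62 and p from 0.15 to 0.11. Nominal p < 0.05 would need 1.96 × 0.0933 = 18 points.

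**3. Chance of stopping.** Exact binomial, 50 versus 50, stop if the arms differ by 7 or more survivors (7/50 = 14 points).
- No effect, 68% in both arms: 16.3% in either direction (13.3% to 18.2% for survival of 75% down to 61%); 8.1% in favour of cEEG only.
- 61% versus 75%: 54.6%. The chance of p < 0.05 on the 100 patients is 32.1%, so 0.321 / 0.546 = 59% of stops are nominally significant. The mean estimate at a stop for benefit is 20.7 points when the truth is 14.

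**4. Whole design.** If not stopped, a final pooled z test at 1.96 with 174 per arm. The chance of no stop and final significance is 2.8% under no effect and 30.4% under the planned effect.
- *Test p < 0.05 at the stop, 100 patients.* Type I error 4.9% + 2.8% = 7.7%; power 32.1% + 30.4% = about 63%.
- *Stop counted as a positive result.* Type I error 16.3% + 2.8% = 19.1%; power 54.6% + 30.4% = 85%.
- *Test p < 0.05 at the stop, all patients recruited by then.* Six-month status of the 100th patient arrives after about 100 + 6 × 350/24 = 187.5 recruits at uniform accrual, taken as 94 per arm. By simulation, type I error is about 6.2% and power about 73%.

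| What a stop leads to | Type I error, either direction stops | Type I error, only cEEG benefit stops | Power |
|---|---|---|---|
| p < 0.05 tested on 100 | 7.7% | 6.4% | 63% |
| p < 0.05 tested on about 188 | about 6.2% | between 5% and 6% | about 73% |
| Stop is the positive result | 19% | 12% | 85% |
| No interim look | 5.0% | – | 80% |

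**5. Conventional boundaries at the same look.**
- Haybittle-Peto, two-sided p < 0.001: z = 3.29, and 3.29 × 0.0933 = 31 points. With the final test at 1.96, type I error is 5.0% at 68% survival (5.0% to 5.2% over 61% to 75%, much the same as with no look), power 80.3%, and the chance of stopping under the planned effect 3.5%.
- Lan-DeMets O'Brien-Fleming type, 0.025 per side, information fraction 100/348 = 0.287: z = 4.02, and 4.02 × 0.0933 = 37.5 points. Power is again 80.3%.

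**The case against.** Four points can fairly be made for the protocol.

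*A stop is not a claim.* The text only ends the trial and does not say that a stop means success. This stands, so the 19% figure rests on an assumption that the protocol does not make. But if a stop is not a claim, the 0.05 test must be met at the stop, and power is then 63% to 73%.

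*The direction may be implied.* Section 11.1 frames the hypothesis as improved survival with cEEG, so only a benefit might have been meant. That would halve the chance of stopping under no effect to 8%. But the rule speaks neutrally of the two arms, and section 2.9 lists early evidence of harm as well as benefit as a ground for ending the study. The direction is unsettled.

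*Patients beyond the first 100 would be analysed.* This is plausible, because the analysis is by allocated group, and it is the mildest case in either direction. It still misses both targets.

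*The statistical analysis plan may repair this.* That plan is not shown. The protocol itself fixes the threshold in two sections, so this is not a detail left open.

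A reader might also infer that the rule both raises the false positive rate to 19% and destroys the 80% power. The protocol does not support that: the two harms belong to different readings of a stop. Where type I error is 19%, power rises to 85%. Where power falls to 63%, type I error is 7.7%.

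**Conclusion.** The concern holds in this form: the 14-point rule is a noise-level threshold and not an alpha-controlled boundary, and no reading tried gives the error rate and power stated in section 11.2 together. Type I error at 68% survival ranges from just above 5% (benefit-only stopping, later recruits analysed) to 19% (either direction, stop taken as success). Power is 63% to 73% when the 0.05 test is kept. It exceeds 80% only when the stop is itself the claim, at a type I error of 12% to 19%.

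The figures assume 50 per arm at the look, 174 per arm at the end, pooled z tests and the survival rates of section 11.2. The figure of about 188 patients also assumes uniform accrual without a pause. The 1.5 standard errors depend on none of the readings and change little with the survival rate. Since the rule acts on the primary outcome and can end the trial by itself, it should be corrected before the look is taken.

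**What to change.** In sections 11.3 and 11.4.4, replace the 14-point rule with an alpha-preserving boundary. The simplest is Haybittle-Peto: stop only if the two-sided p value for six-month survival is below 0.001, and test at 0.05 at the end. The Lan-DeMets O'Brien-Fleming type boundary (z about 4.0) is an alternative, or the efficacy stop can be deleted.

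The same wording should state:
- which direction or directions can stop the trial;
- that the look is taken when the 100th patient reaches six months, since recruitment alone does not give six-month survival;
- which patients are analysed if the trial stops, and what conclusion a stop supports.

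The cost is amendment wording only, and the 348 patients can stand. The downside is that the trial will rarely stop early: about 3.5% of the time under the planned effect with Haybittle-Peto, against 55% under the present rule.

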#### **11.4.5. Safety analysis**

Not foreseen.

#### **11.4.6. Deviation(s) from the original statistical plan**

Any deviation from the planned analyses will be justified and reported in the intermediate and final clinical study report.

### **11.5 Handling of missing data and drop-outs**

Lost to follow up and drop outs rate is estimated around 1-2%. Dropout patients are defined as : i) patients who refuse or withdraw consent to participate in the trial ii) patients whom representative refuse or withdraw consent, iii) randomized patients for whom the intervention did not start iv) Patients for whom new information regarding one of the eligibility criteria arise during intervention (i.e. delayed knowledge about previous epileptic seizures/SE or statement of wishes or need for invasive procedure).

Dropout patients will be replaced except those who withdraw consent /patients whom representative withdraw consent as partial analyzable data is available

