#### Exclusion criteria:

- Clinical and/or electrographic *status epilepticus* < 96h before randomization
- Clinical and/or electrographic seizure < 36h before randomization
- Palliative care situation, in which detection of SE or seizures would not have any impact on the patient's care.
- High likelihood of needing a surgical intervention or an invasive diagnostic procedure within the next 48 hours according to the treating physician (as this would require cEEG removal).

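### Section 11.5 replaces randomised patients whose EEG never started or whose eligibility is later questioned, which conflicts with the by-allocation primary analysis

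*Protocol*

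**What the plan says.** Section 11.5 lists four kinds of dropout. The first two concern refused or withdrawn consent. The third and fourth are: "randomized patients for whom the intervention did not start iv) Patients for whom new information regarding one of the eligibility criteria arise during intervention". Three examples are given for the fourth: late knowledge of earlier seizures or status epilepticus, a statement of wishes, and the need for an invasive procedure. The section continues: "Dropout patients will be replaced except those who withdraw consent". The reason given for that exemption is that consent withdrawals leave part of their data usable.

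Other sections set a different rule:
- 11.4.1 forms the analysis groups by allocation: "one of patients allocated to cEEG, the other to those allocated to rEEG".
- 11.3 states: "The discontinuation criteria for patients are the post hoc or proxy consent refusal/withdrawal, only".
- 7.4, 8.3 and 8.5 keep patients whose intervention is interrupted in the study. 7.4 and 8.5 say they are analysed as intention to monitor.
- 8.7 places no limit on concomitant interventions and lets cEEG be paused for an urgent diagnostic procedure.
- 7.1 excludes patients likely to need surgery or an invasive procedure, for one stated reason: "as this would require cEEG removal".
- 3.7 says that treating physicians and electroencephalographers are not blinded.

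**The concern.** The protocol holds two incompatible rules on who is in the primary analysis. A patient who needs an invasive procedure on day 2 can be read as an interrupted case who stays in (8.3, 8.5) or as a dropout to be replaced (11.5). Staff who know the allocation would choose between the two.

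The choice could depend on arm. The reason for the invasive-procedure criterion is removal of the cEEG electrodes, which has less force for a patient between two short routine recordings. Section 3.1 also describes cEEG as resource consuming and says Swiss hospitals cannot offer it to all such patients, so failure to start could be more common in that arm. A patient who dies before the EEG starts would, read literally, fall into the third category.

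At stake is whether the 6-month mortality comparison is still protected by randomisation. If replaced patients are not followed up, their outcomes may be hard to recover later. The protocol accepts the principle elsewhere: section 2.7 keeps the data of patients who die before consent, to avoid biasing the study.

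**Working it through.** **1. The plan's own figure.** Inputs from 11.2: two-sided alpha 0.05 and power 0.80, with the target given as "2x174 patients (348 in total) would be needed to detect a difference of 61% versus 75% in survival". With pooled variance and no continuity correction, and mean survival (0.61 + 0.75)/2 = 0.68:

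n = [1.96·√(2·0.68·0.32) + 0.842·√(0.61·0.39 + 0.75·0.25)]² / 0.14² ≈ 173.1, rounded up to 174 per arm.

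This matches the plan. Power at 174 per arm is 0.802. The sample size is not in dispute.

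**2. Does replacement mean exclusion?** Section 11.5 does not say so outright. It exempts consent withdrawals because their data are partly usable, which makes sense only if the replaced patients supply none. Replacement would do no harm to the comparison if the original patients were kept. The harm comes from that implication.

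**3. Size if patients are removed from one arm.** Suppose true mortality is p in both arms, and a share f of one arm, with mortality m, is removed and replaced, so that 174 per arm are analysed.
- Mortality left in that arm: p′ = (p − f·m)/(1 − f).
- Spurious difference: d = p − p′ = f·(m − p)/(1 − f).
- Rejection rate: Φ((d − 1.96·se₀)/se₁) + Φ((−d − 1.96·se₀)/se₁), with se₀ = √(2·p̄(1 − p̄)/174), p̄ = (p + p′)/2, and se₁ = √((p(1 − p) + p′(1 − p′))/174).

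Example with p = 0.32, f = 0.05, m = 1: p′ = 0.27/0.95 = 0.284, d = 3.6 points, rejection rate 0.112.

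Here p is 39% (the plan's control rate) or 32% (the mean of 39% and 25%). The values of f and m are assumptions, with m from 60% to 100%.

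| Share removed, one arm | p = 39%: points | type I error | p = 32%: points | type I error |
|---|---|---|---|---|
| 2% | 0.4–1.2 | 0.051–0.057 | 0.6–1.4 | 0.052–0.059 |
| 5% | 1.1–3.2 | 0.055–0.095 | 1.5–3.6 | 0.060–0.112 |
| 10% | 2.3–6.8 | 0.073–0.261 | 3.1–7.6 | 0.097–0.346 |

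For scale, the difference needed for p < 0.05 at 32% mortality is 1.96·√(2·0.32·0.68/174) = 9.8 points. If m equals p there is no bias, and if m is below p the sign reverses.

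**4. What the protocol's rate tells us.** Section 11.5 puts loss to follow-up and dropout together at 1–2%. Of the planned intake ("It is expected to randomize 350 patients over a 2 year-recruiting period") that is 3.5 to 7 patients over both arms and all causes. Section 11.4.1 traces the same 1–2% to loss to follow-up in a post-cardiac-arrest registry, so it is not an estimate of the third and fourth categories.

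**5. Cost of keeping these patients.** Assume a share f of the cEEG arm goes unmonitored and has 61% survival. Expected cEEG survival is then 0.75(1 − f) + 0.61f.

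| f | Survival | Power at 174 per arm | n per arm for 80% power |
|---|---|---|---|
| 1% | 74.86% | 0.794 | 177 |
| 2% | 74.72% | 0.785 | 181 |
| 5% | 74.30% | 0.758 | 194 |
| 10% | 73.60% | 0.709 | 217 |

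**The case against.** The strongest reply is that 11.5 orders replacement and never states that these patients leave the primary analysis. The only group expressly excluded from it is those lost to follow-up (11.4.1), and the analysis plan may settle the set. This stands in part: exclusion is inferred from the reason given for the exemption. But the protocol itself fixes the replacement rule and the reason, and they conflict with other sections, so the text still needs reconciling.

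A reader might infer that patients will be lost from the cEEG arm only. The text does not support that. The rule is worded for both arms, the control recordings also span 24 to 48 hours (8.1), and a cEEG patient can be paused for a diagnostic procedure and kept. Randomisation just before the intervention (6.2.1, 7.3) also limits failures to start.

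A reader might also infer a bias in favour of cEEG. That is unproven: an EEG may not start because a patient improved, and nothing in the protocol shows that patients who need a procedure have above-average mortality.

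Nor are all the fourth-category examples events after randomisation. Earlier seizures and a statement of wishes predate it, and only their discovery could differ by arm. The need for a procedure is the one that can truly arise afterwards.

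Finally, at the stated 1–2% the effect is small. That is correct if the rate covers these two categories, which its source does not show.

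**Conclusion.** The contradiction is real. Followed as written, 11.5 undermines the by-allocation primary analysis of an open-label mortality trial. Three things limit the point: exclusion is implied and not stated, differential removal is possible and not shown, and its direction is not established.

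The size depends on a number that the protocol does not give. Removing 2% of one arm would produce at most about 1.4 points and a type I error of 0.059. The effect becomes material only at about 5–10% of one arm, an assumed range, with removed patients at 60–100% mortality, also assumed. The case for changing the text rests on the conflicting rules and the low cost of repair, and does not need a large predicted bias.

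**What to change.** Reconcile 11.5 with 7.4, 8.3, 8.5, 11.3 and 11.4.1:
- State that patients whose intervention did not start, and those with late eligibility information, stay in the intention-to-monitor set in their allocated arm and are followed for 6-month mortality.
- State that any extra recruits are added to these patients and do not substitute for them.
- Limit removal to refused post-hoc or proxy consent and to a late-found statement of wishes against participation, and report the numbers by arm. The second exception is needed because 2.7 bars patients known to have objected, and allows proxy consent, or use of a deceased patient's data without consent, only where no statement of wishes exists.
- Apply the remaining exclusions only in the per-protocol analysis already planned in 11.4 and 11.4.1.

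The cost is amended wording, a few extra follow-up calls, and slight dilution. Under the assumptions in the last table, power is about 0.79 against 0.80 when 1–2% of the cEEG arm is unmonitored. Restoring 80% would take about 3 to 7 more patients per arm (177 or 181 against 174).

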## **12. QUALITY ASSURANCE AND CONTROL**

### **12.1 Data handling and record keeping / archiving**

#### **12.1.1 Case Report Forms**

All trial data of each patient will be recorded from the source documents in a secured electronic Case Report Form (eCRF, secuTrial® software) independently managed by the Clinical Trial Unit, Lausanne, warranting data integrity, security, quality and traceability. Only authorized study collaborators (delegated by the local investigator at each site) will be allowed to proceed to eCRF entries/modifications. eCRFs will be kept current to reflect patient status at each phase during the course of study. Participants must not be identified in the eCRF by name or initials and birth date. Appropriate coded identification must be used according to study-specific standard operating procedures elaborated by the sponsor-coordinating investigator.

Both EEG quantitative analysis and general hospitalization costs assessments will not be reported in the eCRF as these evaluations will be done at the end of the study and directly integrated in the clinical trial database following a data entry validation procedure.

#### **12.1.2. Specification of source documents**

Source data must be available at each site to document the existence of the study participants. Source data must include the original documents relating to the study. The electronic patient medical file will consist in the source data at all sites. The only exceptions will be:

- The dates/signatures of the Informed consent forms
- The randomization number and intervention allocation (attributed by the web-based randomization system following a randomization list)
- The SAE assessment (using a study-specific paper SAE form)
- The 6-month phone interview (data collected on a paper form – for blinding reasons).

All paper source data will be archived at site in the Investigator Site File (ISF).

EEG traces will be stored in the clinical EEG database of each center, as clinical information deriving from it will be readily accessible to treating clinicians, and as interpretations will be written as in clinical practice on the same day of recording. Routinely, after the interpretation of each recording, related videos will be deleted. In a small proportion of patients (<5%) it is general practice to save short video-clips of salient clinical events (some seconds to a few minutes in total) for subsequent clinical judgment, according to the clinical evolution. These files are separated from the original (now video-less) recording. If every video had to be deleted for this study, this would expose participating patients to a limitation regarding their clinical care, as compared to patients not participating at the study; we feel that this would be ethically unacceptable.

